#### Composite outcome measures

We will also use data from the above outcome measures to create a series of composite outcome measures (see analysis section for further details).

### Ascertainment of outcomes

#### Clinical outcomes

During the first three months of the study we worked with the company that produce Quest Browser software  to develop computerised queries that would produce precisely the same types of data as we have used in our pilot study of primary outcome measures that used QRESEARCH practices . We also worked with the company to produce the outputs needed for the secondary outcome measures.

For each practice agreeing to be involved in the trial, Quest Browser software was installed on their clinical computer system. At the time of installation of the software, a search of the GP computer system, using Quest Browser was undertaken to provide anonymised baseline data and details of individual patients at risk from potentially hazardous prescribing and medicines management.

Anonymised and encrypted data pertaining to the computerised primary and secondary outcomes measures are sent via the Internet to a secure computer at the University of Nottingham. Using Quest Browser Central software the anonymised data are automatically imported in an Access database along with a unique code identifying the practice.

Further data are collected at six and 12 months after the completion of the 12-week intervention period in practices in each arm of the trial.

#### Issues concerning ascertainment of secondary clinical outcome measures

Over the course of the study we have identified issues that may limit the validity of three of our secondary outcome measures.

As already noted, for outcome number six, we have identified seven practices that keep their records of INR results separate from their main practice computer system and thus appear to have very high proportions of patients not having INRs checked according to the computer searches we have used in our study. We will need to exclude these practices from the analysis of this outcome measure.

For outcome number nine, during the course of our study, the NPSA required all GP computer systems to introduce methods of ensuring that electronic prescriptions for methotrexate gave instructions that the medication should be taken weekly[25]. Since this change was introduced our computer searches have been unable to capture the text used to confirm the dosage instructions. Unless we can resolve this problem it is unlikely that we will be able to report on the follow-up data for this outcome measure.

For outcomes nine and 10, we have found that for the eleven practices that use the TPP computer system, we are unable to extract information on dosage instructions. This means that we will not be able to report on these outcome measures for the practices in our trial that use this system.

#### Data for the economic analysis

##### Costs of the intervention

The costs measured at practice level are the costs of setting-up and delivering the intervention. The costs measured at the patient level are any costs of delivering the intervention that can be linked to individual patients. Resources associated with providing the intervention have been recorded, and will be combined with unit costs to produce total costs.

##### Modelling economic analysis

Patients identified from the baseline computer system searches as being at risk of potentially hazardous prescribing and medicines will be included in the modelling economic analysis provided that they give informed consent for researchers to view their records.

Wherever possible, data are extracted electronically, although in the case of correspondence regarding hospital contacts it is usually necessary to anonymise and photocopy relevant information. Anonymised data are sent to the University of Nottingham where data processing and analysis will take place.

Patients in both intervention arms will be followed up for 12 months following the completion of the intervention in each practice. Error-related resource use data will be collected from these patients. NHS resource use data will be collected retrospectively for the 12 month period before the intervention (baseline) and for 12 months after the intervention (follow-up). Unit costs associated with the intervention will be obtained from Personal and Social Services Research Unit , Department of Health  and other reference costs.

#### Data for the qualitative study

Data for the qualitative study have been obtained from:

• 12 initial brief interviews with NHS staff

• 20 in-depth interviews with NHS staff

• Interviews with the six trial intervention pharmacists

• Focus groups involving a total of 30 participants (NHS staff and trial intervention pharmacists)

• Diary records kept by the six trial intervention pharmacists of their activities and experiences

• Interviews with two members of the research team closely involved in roll-out of the trial.

Data generation continued until no new themes or issues were emerging (saturation).

Interviews and focus groups have been digitally recorded and transcribed and accompanying field notes have been retained.

The specific research questions explored in the qualitative study include the following:

• What are the views of primary care staff and pharmacists about the acceptability, effectiveness and long-term sustainability of the trial interventions?

• What barriers, if any, were experienced by trial pharmacists and primary care staff in identifying patients at risk from potentially hazardous prescribing, in correcting these problems once identified, and instituting safer medicines management culture and policies in the pharmacist-led IT-based intervention practice arm?

• What barriers, if any, were experienced by primary care staff in identifying patients at risk from potentially hazardous prescribing, in correcting these problems once identified, and instituting safer medicines management culture and policies in the simple feedback practice arm?

• In which ways might the trial interventions need to be modified or adapted in order to maximise their effectiveness when implemented in routine general practice?

• What alternative interventions might be both acceptable to key stakeholders and effective in reducing potentially hazardous prescribing in general practice?

### Adverse events

A protocol for dealing with serious adverse events that might occur in study practices in patients identified by the PINCER trial outcome measures is shown in Appendix 1 (see additional file 1).

### Sample size

Our sample size calculations are based on the assumption that for the proportion of patients fulfilling the criteria for any one of our primary outcome measures, there will be a maximum 11% reduction in the simple feedback arm and a 50% reduction in the pharmacist intervention arm.

Separate sample size calculations were performed for each of the primary outcome measures (see Table 2). Sample sizes unadjusted for clustering were calculated using the software package nQuery Advisor^® ^version 6.0. [26]

**Table 2 T2:** Sample size calculations for the three primary outcome measures assuming an 11% reduction in error rates for the simple feedback group and a 50% reduction in error rates for the intervention group

Outcome measure	Patients with a history of peptic ulcer who have been prescribed a non-selective NSAID	Patients with asthma who have been prescribed a beta-blocker	Patients aged 75 years and older prescribed an ACE inhibitor or a loop diuretic long-term without a check of their renal function and electrolytes in the previous 15 months
Median error rate^1^ (Interquartile range)	5.76% (3.76% – 7.85%)	1.90% (1.27% – 3.08%)	19.80% (15.13% – 32.69%)

Error rate in control group (assuming 11% reduction)	5.13%	1.69%	17.62%

Error rate in intervention group (assuming 50% reduction)	2.88%	0.95%	9.90%

Intraclass Correlation Coefficient (ICC)^1^	0.01082	0.00657	0.00952

Cluster size^1^	63	439	105

Inflation factor	1.7	3.9	2.0

Total number of practices required	64	66	12

^1 ^Estimated using data obtained from 43 general practices contributing to the QResearch database

Data from 43 general practices contributing anonymous clinical data to the QRESEARCH research database  were used to describe prevalence rates of asthma and peptic ulcer disease and to estimate the median proportions for each of our primary outcome measures. The intracluster correlation coefficients (ICCs) used in the calculation of the design effect (to inflate the sample sizes to adjust for the cluster design)[27] were as follows:

• 0.01082 for patients with a history of peptic ulcer who have been prescribed a non-selective NSAID (excluding those that were also in receipt of PPIs, which would protect against the risks from NSAIDs);

• 0.010657 for patients with asthma who have been prescribed a beta-blocker;

• 0.00952 for patients aged 75 years and older who have been prescribed an ACE inhibitor or a loop diuretic long-term who have not had a computer-recorded check of their renal function and electrolytes in the previous 15 months.

The suggested 11% reduction in the simple feedback arm is the equivalent to the 75% centile for changes observed as a result of audit and feedback in a Cochrane systematic review available at the time that we did our sample size calculations. [28]

The suggested 50% reduction in the pharmacist intervention arm of the trial is based on extrapolation from our pilot studies[18,19] and findings from systematic reviews and other studies that, at the time of applying for funding for our study, showed that:

• Pharmacist-led interventions can lead to resolution of medication-related problems in 55–93% of patients [29-33]

• Educational outreach is a moderately powerful tool for changing professional behaviour[34]

• Multifaceted interventions aimed at different barriers to change are more effective than single interventions[35].

The calculation shown in Table 2 indicates that we would need at least 66 practices to detect a difference between an 11% reduction in error rate in the simple feedback arm and a 50% reduction in the intervention arm for each of our three primary outcome measures.

On the basis of these calculations, we decided to aim to recruit at least 68 practices. With 34 practices in each of the two treatment arms, we would have at least 80% power (two-tailed alpha of 0.05) to demonstrate a 50% reduction in rates of potentially hazardous prescribing and medicines management in the pharmacist-led arm compared with 11% in the simple feedback arm.

### Compliance

We recognise that it can be a challenge to encourage general practices to engage in interventions. However, as the intervention involves either simple feedback, or feedback and the provision of a pharmacist to work with the practices, we do not expect non-compliance with the intervention to be a large problem. In addition, from our experience of the pilot study and of conducting previous trials, we believe that the risks of non-compliance will be minimised by providing practices with clear information on what the study involves, providing access to members of the research team to answer queries and address problems experienced by the practices, and support from the PCTs.

### Likely rate of loss to follow up

We do not envisage practices dropping out of the study once they have agreed to take part. Nevertheless, at the outset we have stressed to the practices the importance of allowing us to collect follow-up data, even if the practice has not engaged fully in one of the interventions. As outcome data collection will require minimal input from the practice or its staff, we do not foresee problems with obtaining outcome data from participating practices.

Some patients will move practices and some will die within the intervention period. However, this is unlikely to have a large impact on the proportion of patients with errors at follow-up, unless leaving the practice or death is differentially related to medication error. This is unlikely because the number of deaths attributable to the medication errors we are studying is likely to be small during the course of the study. Nevertheless, we will try to follow up patients who have died by viewing their electronic medical records up until the time of death, and requesting paper-based records that might contain details of contacts with secondary care.

### Withdrawal of patients from the study

Withdrawal of patients consenting for their medical records to be examined will not affect the analysis of clinical outcomes as these are obtained from anonymised computer searches of all "at risk" patients in the general practices recruited to the study.

Withdrawal of these patients will affect the health economic analysis although it is expected that numbers of patients withdrawing will be small. A patient will be considered to have withdrawn from the study if the study team receive any notification that the patient wishes to withdraw. This notification might come from the patient themselves, the patient's representative or from the patient's general practice.

### Statistical analysis

Data analysis, using the following analysis plan, will be undertaken blind to treatment arm allocation (i.e. the treatments will be identified only as A and B until analysis is complete). The primary analysis for the clinical outcomes used in the trial will be undertaken using the six-month follow-up data.

### Descriptive analyses

Continuous data will be explored using frequencies and histograms and described using means and standard deviations (SD) if approximately normally distributed and medians and inter-quartile ranges (IQR) if non-normally distributed. Categorical data will be described using frequencies and percentages. Characteristics of participating practices will be compared informally between treatment arms.

#### Describing baseline characteristics of patients and practices

a) The following characteristics will be described by treatment arm:

i) Patient age and gender

ii) Practice list size (median and IQR, or mean and SD if normally distributed)

iii) Practice population by age group (number and %)

iv) Practice deprivation using the Index of Multiple Deprivation (IMD) 2004[36] (median and IQR, or mean and SD if normally distributed) Note this has been calculated by multiplying the proportion of the total list size living in each Lower Layer Super Output Area (LSOA) by IMD 2004 LSOA level score and then summing these across all LSOAs in which patients registered at the practice live.

v) Practice training status (%)

vi) Practice Quality and Outcomes Framework (QOF) medicines management indicator points and total QOF points[37] if available (Mean (SD or median (IQR) dependent on distributions).

#### Describing baseline prevalence of medication-related problems

The following will be described using the numerator, denominator and percentage by treatment arm, at patient level:

i) Primary outcome measures:

Patients with a history of peptic ulcer prescribed an NSAID without a PPI (numerator)/

Patients with a history of peptic ulcer without a PPI (denominator)

Patients with asthma prescribed a beta-blocker (numerator)/Patients with asthma (denominator)

Patients aged ≥75 on long term ACE inhibitors or diuretics without urea and electrolyte monitoring in the previous 15 months (numerator)/

Patients aged ≥75 on long term ACE inhibitors or diuretics (denominator)

ii) Secondary outcome measures:

Patients with asthma and not CHD prescribed a beta-blocker (numerator)/

Patients with asthma and not CHD (denominator)

Female patients with a history of venous or arterial thromboembolism and arterial thrombosis prescribed combined oral contraceptives (numerator)/

Female patients with a history of venous or arterial thromboembolism and arterial thrombosis (denominator)

Patients prescribed methotrexate for ≥ three months without a full blood count in last three months (numerator)/

Patients prescribed methotrexate for ≥ three months (denominator)

Patients prescribed methotrexate for ≥ three months without an liver function test in last three months (numerator)/

Patients prescribed methotrexate for ≥ three months (denominator)

Patients prescribed warfarin for ≥ three months without an INR in last three months (numerator)/

Patients prescribed warfarin for ≥ three months (denominator)

Patients prescribed lithium for ≥ three months without a lithium level in last three months (numerator)/

Patients prescribed lithium for ≥ three months (denominator)

Patients prescribed amiodarone for ≥ six months without a thyroid function test in the last six months (numerator)/

Patients prescribed amiodarone for ≥ three months (denominator)

Patients prescribed methotrexate without instructions to take weekly (numerator)/

Patients prescribed methotrexate (denominator)

Patients prescribed amiodarone for ≥ one month at a dose >200 mg/day (numerator)/

Patients prescribed amiodarone for ≥ one month (denominator)

Four composite outcome measures will also be used comprising:

Number of patients with at least one prescribing problem (numerator)/

Number of patients at risk of at least one prescribing problem (denominator)

Number of patients with at least one monitoring problem (numerator)/

Number of patients at risk of at least one monitoring problem (denominator)

Number of patients with at least two prescribing problems (numerator)/

Number of patients at risk of at least two prescribing problems (denominator)

Number of patients with at least two monitoring problems/

Number of patients at risk of at least two monitoring problems (denominator)

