### Outcome measures

Outcome measures are measured at the following two time points:

• Six months after the end of the intervention period

• 12 months after the end of the intervention period.

A summary of the main outcome measures is shown Table 1. The measures are described in more detail below.

**Table 1 T1:** Summary of main outcome measures used in the trial

Outcome measure number	Brief description of outcome measure
1	Patients with a history of peptic ulcerwho have been prescribed a non-selective NSAID

2	Patients with asthmawho have been prescribed a beta-blocker

3	Patients aged 75 years and older who have been prescribed an ACE inhibitor or a loop diuretic long-term who have not had a computer-recorded check of their renal function and electrolytes in the previous 15 months

4	Proportions of women with a past medical history of venous or arterial thrombosis who have been prescribed the combined oral contraceptive pill

5	Patients receiving methotrexate for at least three months who have not had a recorded full blood count and/or liver function test within the previous three months

6	Patients receiving warfarin for at least three months who have not had a recorded check of their INR within the previous 12 weeks

7	Patients receiving lithium for at least three months who have not had a recorded check of their lithium levels within the previous three months

8	Patients receiving amiodarone for at least six months who have not had a thyroid function test within the previous six months

9	Patients receiving prescriptions of methotrexate without instructions that the drug should be taken weekly

10	Patients receiving prescriptions of amiodarone for at least one month who are receiving a dose of more than 200 mg per day

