#### Primary outcome measures

We are using the following primary outcome measures based on proportions of:

1. Patients with a history of **peptic ulcer **who have been prescribed a non-selective **NSAID**:

• More specifically, those with a computer-coded diagnosis of peptic ulcer disease, at least six months prior to data collection, who have a computer record for one or more prescriptions for a non-selective NSAID in the six months prior to data collection who have not also had a prescription for a PPI within that six month period

• It should be noted that the denominator for this outcome measure is patients with a computer-coded diagnosis of peptic ulcer disease, at least six months prior to data collection, who have not also had a prescription for a PPI in the six months prior to data collection.

2. Patients with **asthma **who have been prescribed a **beta-blocker**:

• More specifically those with a computer-coded diagnosis of asthma, at least six months prior to data collection, who have a computer record of one or more prescriptions for a beta-blocker (oral preparations or eye drops) in the six months prior to data collection

• The denominator for this outcome measure is patients with a computer-coded diagnosis of asthma, at least six months prior to data collection.

3. Patients **aged 75 years and older **who have been prescribed an **ACE inhibitor or a loop diuretic **long-term (see below) who have not had a computer-recorded check of their renal function and electrolytes in the previous 15 months:

• More specifically, long-term prescribing implies a first prescription for an ACE inhibitor or a loop diuretic at least 15 months before the time of data collection and at least one prescription in the six months beforehand

• The denominator for this outcome measure is patients aged 75 years and older who have been prescribed an ACE inhibitor or a loop diuretic long-term according to the above definition.

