#### Inadequate monitoring

These outcomes are based on proportions of:

5. Patients receiving **methotrexate **for at least three months who have not had a recorded full blood count and/or liver function test within the previous three months

• More specifically

5a: patients with one or more prescriptions for methotrexate recorded on computer three to six months prior to data collection *and *in the three months prior to data collection who have not had a computer-recorded full blood count within the previous three months

5b: patients with one or more prescriptions for methotrexate recorded on computer three to six months prior to data collection *and *in the three months prior to data collection who have not had a computer-recorded liver function test within the previous three months.

6. Patients receiving **warfarin **for at least three months who have not had a recorded check of their INR within the previous 12 weeks

• More specifically, patients with one or more prescriptions for warfarin recorded on computer three to six months prior to data collection *and *in the three months prior to data collection who have not had a computer-recorded INR within the previous three months.

7. Patients receiving **lithium **for at least three months who have not had a recorded check of their lithium levels within the previous three months

• More specifically, patients with one or more prescriptions for lithium recorded on computer three to six months prior to data collection *and *in the three months prior to data collection who have not had a computer-recorded lithium level within the previous three months.

8. Patients receiving **amiodarone **for at least six months who have not had a thyroid function test within the previous six months

• More specifically, patients with one or more prescriptions for amiodarone recorded on computer 6–12 months prior to data collection and in the three months prior to data collection who have not had a computer-recorded thyroid function test within the previous six months.

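### Secondary outcome 8: the listed denominator (amiodarone for three months or more) does not match its numerator or its definition (six months or more)

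*Protocol article*

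**What the plan says.** Table 1 of the protocol article defines outcome 8 as "Patients receiving amiodarone for at least six months who have not had a thyroid function test within the previous six months". The section Inadequate monitoring turns this into a search rule: one or more amiodarone prescriptions "recorded on computer 6–12 months prior to data collection and in the three months prior to data collection", with no thyroid function test in the last six months. That section gives no separate denominator.

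The only explicit denominator for outcome 8 is in Describing baseline prevalence of medication-related problems. There the numerator keeps the six-month treatment requirement, but the next line reads "Patients prescribed amiodarone for ≥ three months (denominator"). The section Describing outcome data then says that the listed measures will be reported by arm, with numerators, denominators and percentages, at six and 12 months.

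Two other wording differences concern the same measures:

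- **Outcome 3 (primary).** The list has "Patients aged ≥75 on long term ACE inhibitors or diuretics (denominator"). The section Primary outcome measures has patients "prescribed an ACE inhibitor or a loop diuretic long-term according to the above definition".
- **Outcome 6 (secondary).** Table 1 counts patients who "have not had a recorded check of their INR within the previous 12 weeks". The search rule counts patients "who have not had a computer-recorded INR within the previous three months", and the list also uses three months.

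**The concern.** A proportion needs a numerator drawn from its denominator, with every member of the denominator able to enter the numerator. As listed, outcome 8 fails the second condition. Patients on amiodarone for three to under six months are in the denominator, but the numerator's own duration rule shuts them out. They would be recorded as free of error whatever their monitoring.

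This line is the only stated denominator, so an analyst could reasonably build the at-risk set from it. That would understate the reported percentage at every time point. In the patient-level logistic model of Comparisons between treatment arms, the ineligible patients would be coded as non-events. The composite monitoring measures are built on patients at risk of a monitoring problem, so they could inherit the same set.

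**Working it through.** **1. Is the mismatch a convention of the list?** The duration-based pairs in the list are:

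| Measure | Numerator | Denominator |
|---|---|---|
| Methotrexate, full blood count | ≥3 months | ≥3 months |
| Methotrexate, liver function | ≥3 months | ≥3 months |
| Warfarin, INR | ≥3 months | ≥3 months |
| Lithium, level | ≥3 months | ≥3 months |
| Amiodarone, thyroid function | ≥6 months | **≥3 months** |
| Amiodarone, dose | ≥1 month | ≥1 month |

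Five of the six pairs match; outcome 8 alone does not. The article has no search rule for a three-month amiodarone group, so the line looks like a slip and not a deliberate choice.

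**2. Effect on the percentage.** Let N6 be the patients treated for at least six months, X those among them without the test, and M the patients treated for three to under six months. The intended proportion is p = X/N6. The listed one is X/(N6 + M). With f = M/(N6 + M), the listed proportion equals p × (1−f).

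Neither p nor f is in the article. Assuming p = 40%:

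- f = 5%: 40% × 0.95 = 38%
- f = 10%: 40% × 0.90 = 36%
- f = 20%: 40% × 0.80 = 32%

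Assuming p = 30%, the same values of f give 28.5%, 27% and 24%.

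**3. Effect on the comparison between arms.** If f is the same in both arms, the factor (1−f) cancels from the risk ratio but not from the odds ratio. Assume true rates of 40% and 30%:

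| f | Rates | Risk ratio | Odds ratio | Difference |
|---|---|---|---|---|
| 0 | 40% v 30% | 1.33 | (0.40/0.60)/(0.30/0.70) = 1.56 | 10 points |
| 5% | 38% v 28.5% | 1.33 | (0.38/0.62)/(0.285/0.715) = 1.54 | 9.5 points |
| 20% | 32% v 24% | 1.33 | (0.32/0.68)/(0.24/0.76) = 1.49 | 8 points |

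**4. Is any sample-size figure touched?** Outcome 8 has no power calculation. The only figure tied to a measure discussed here is the 12 practices for outcome 3 in Table 2. Inputs from Table 2 and Sample size: median error rate 19.80%, reductions of 11% and 50%, ICC 0.00952, cluster size 105, two-sided alpha 0.05, power 80%.

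- Rates: 0.198 × 0.89 = 17.62% and 0.198 × 0.50 = 9.90%
- Two-proportion formula without continuity correction: 312 patients per arm
- Design effect: 1 + (105 − 1) × 0.00952 = 1.99
- Practices per arm: 312 × 1.99 / 105 = 5.91, rounded up to 6, so 12 in total, as stated

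The sample-size section describes this measure with the loop-diuretic wording, so nothing there needs to change.

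**5. Outcome 6.** Twelve weeks is 84 days and three months is about 91. A patient last tested 85 to 91 days before data collection changes status with the rule used. The list and the search rule both say three months. The 12-week wording is in Table 1 and in the summary line above the search rule.

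**The case against.** The strongest reply is that this is a one-line slip with little consequence. Outcome 8 is an unpowered secondary measure, and the article treats secondary analyses as partly exploratory. The list sits under baseline description, and the section on comparisons does not restate its denominators. The queries had already been built and used for the baseline extraction, and nothing shows that they followed the list and not the search rule. With f similar in both arms, the treatment comparison barely moves. All of this stands, and it limits the weight of the point. It does not remove the contradiction, because the list is expressly carried to follow-up and no other text gives this denominator.

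A reader might also infer that the list redefines a primary outcome by widening loop diuretics to all diuretics. The documents do not support that. Primary outcome measures gives an explicit loop-diuretic denominator, and long-term use is defined only for ACE inhibitors and loop diuretics. The statistical section Primary outcomes repeats the loop wording. The list abbreviates elsewhere too, shortening the non-selective NSAID of outcome 1 to NSAID. Numerator and denominator for outcome 3 agree with each other. Shorthand is the most plausible reading.

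Nor does outcome 6 show the list departing from the definitions: the list agrees with the operative search rule. The difference there lies between summary and specification.

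**Conclusion.** The outcome 8 denominator is wrong as written. Followed literally, it understates the percentage by the factor (1−f). The 38% to 32% range for a true 40% rests on an assumed f of 5% to 20% and an assumed true rate; the article gives neither. A reader might infer a materially biased treatment effect, but that does not follow. With equal f the risk ratio is unchanged, and in the example the odds ratio falls from 1.56 to no lower than 1.49. Equal f is itself an assumption, reasonable in expectation under randomisation. Any effect on the monitoring composites cannot be sized from the article.

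No power or sample-size figure is affected. The wording of outcomes 3 and 6 is a minor editorial matter.

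**What to change.** 1. In Describing baseline prevalence of medication-related problems, set the outcome 8 denominator to the six-month population of the search rule: an amiodarone prescription 6–12 months before data collection and another in the three months before it.
2. Check that the extraction query, the analysis code and the at-risk sets for the monitoring composites use that population.
3. Editorial: restore the word loop before diuretics in both outcome 3 lines of the list.
4. Editorial: reconcile the 12-week wording for outcome 6 (Table 1 and the summary line) with the three-month search rule and list, so that one window is stated throughout.

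The cost is a few words of text and a check of query and code. The article states that analysis had not yet been undertaken, so the denominator can be settled before results are seen.
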